## 1. SUMMARY

**Rationale:** Approximately, 10-20% of older adult patients present with non-specific complaints (NSCs) at the emergency department (ED). NSCs are known as poorly described symptoms, such as 'weakness' and 'fatigue', often leading to an extensive differential diagnosis. Almost half of patients presenting with NSCs suffer from a serious underlying illness. Currently, a management protocol for patients with NSCs does not exist. Patients with NSCs are often under triaged, stay longer at the ED (ED-LOS) or hospital (HOSP-LOS) and are at a higher risk for complications during hospitalisation. A special care pathway for patients with NSCs was designed to resolve some of these problems and improve the efficiency of care at the ED.

**Objective:** To implement and evaluate a care pathway for older adults presenting with non-specific complaints at the emergency department.

**Study design:** A longitudinal multi-centre cohort with a stepped-wedge cluster design.

**Study population:** Older adults  $\geq 70$  years of age presenting with NSCs at the practice of the general practitioner (GP), the elderly care physician at a nursing home or the emergency department of the hospital will be evaluated for inclusion. Data from control patients will be collected retrospectively.

**Recruitment:** Recruitment will take place during workdays between Monday – Friday from 11:00 am – 20:00 pm and comprise of a study period of 6 months, according to the study protocol. The primary health care provider (such as a GP or elderly care physician at a nursing home) will indicate whether a patient is eligible for access to the care pathway and inform the specialist at the ED. Every referring care professional will have a card, which provides information on how to refer a patient to the care pathway and to whom. Patients can also enter the care pathway after triage at the ED, if the main complaint is non-specific. If the ED specialist registers access to the care pathway and the patient gives consent, the patient will be included and baseline data collected.

**Intervention:** If feasible, an ED-coach (passive or active form) will be appointed to each participant of the care pathway. The NSC will be evaluated in-depth, the patient will undergo APOP-screening during triage and if indicated, a comprehensive geriatric assessment will be performed after discharge from the ED at another department. The patient will be seen by a specialist or experienced resident in training at the ED, who will order a standard set of diagnostic tests and review the results. The APOP-risk score will guide further actions in the care pathway. A verification of the medication list will be performed <24 hours and a review of the medication will follow during admission.

**Control cohort:** Recruitment of controls will occur before implementation of the care pathway and on workdays between Monday – Friday from 11:00 am – 20:00 pm. The study period is estimated at approximately 6 months, according to study protocol. Each participating hospital will inform participants regarding their policy on data collection prior to implementing the care pathway. Data for controls within hospitals with access to CTcue will be collected retrospectively. The other participating hospitals will include eligible patients prospectively for the same estimated study period. After 30 days, the research nurse will evaluate complications that occurred after the patient leaves the care pathway.

**Main study parameters/endpoints:** Main endpoints are to evaluate the length of stay at the ED (ED-LOS) and exploring patient satisfaction on 4 established domains. Secondary objectives are evaluating the length of stay at the hospital (HOSP-LOS), discharge destination, medical diagnosis (at admission versus discharge), frequency of readmissions / revisits, 30-day mortality, loss of functional

status and costs-effectiveness of the care pathway. Study parameters are age, gender, main non-specific complaint, main diagnosis at ED-arrival and discharge, way of arrival (per ambulance, public transportation, etc.), main domain of NSC (somatic, nutrition, psychosocial, functional, mobility, falls), living situation (independent, care at home), diagnostic tests, specialist seeing the patient and consulting specialists and ED-logistics (time of arrival at ED, duration of triage, triage colour).

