## **4. METHODS**

### **STUDY DESIGN**

The following organizations will implement the care pathway:

- Catharina Ziekenhuis, Eindhoven, the Netherlands
- ETZ (Elisabeth-TweeSteden Ziekenhuis), Tilburg, the Netherlands
- Jeroen Bosch Ziekenhuis, 's Hertogenbosch, the Netherlands
- Maxima Medisch Centrum, Veldhoven, the Netherlands
- St. Anna ziekenhuis, Geldrop, the Netherlands
- General practitioners of the Brabant area
- Nursing homes

Optional hospitals:

- Amphia, Breda, the Netherlands

Inclusion will take place during approximately 6 months after initiation of the study on workdays between Monday – Friday from 11:00 am – 20:00 pm.

The first hospitals were planned to initiate the study and start implementation of the care pathway and data collection in December 2019 or at the earliest possibility after approval of the study protocol. Due to the COVID-pandemic and its burden on hospital-care throughout the Netherlands, implementation could not take place as planned. The Jeroen Bosch Hospital had started the care-pathway, but had to discontinue after a few weeks due to the massive burden of COVID-care.

Considering that the COVID-pandemic, which resulted in a drop of regular care, may have had an influence on the processes in the ED and the number of elderly people presenting with non-specific complaints, it was decided to temporarily withhold the inclusion of control patients and implementation of the care-pathway. The estimation was made that the COVID-pandemic would be a great confounder in results when comparing a pre-pandemic and post-pandemic population. Therefore it was decided to start over with inclusion of the control-group. In July and August 2020 the participating hospitals were consulted and asked if they had resumed their usual care and how their ED and population had changed. All hospitals agreed to restart inclusion of the control-group from August 2020 onward. Since the numbers of elderly people with non-specific complaints are

expected to be lower than before the COVID-pandemic, it is possible that the period for inclusion for the control group has to be extended. The planned start for implementation of the care-pathway is January 2021, dependent on inclusion of the control-group and the evolution of the COVID-pandemic.

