At this moment, October 2020, we are experiencing a second wave of the COVID-pandemic throughout the Netherlands. During the first outbreak, the hospitals in Noord-Brabant especially were in state of crisis, with a drop in the rates of regular care. With this impact in mind, we decided to withhold the care-pathway and include a post-COVID control-group. However, the global opinion is becoming that COVID is here to stay, and it will become part of the day to day business both at social and hospital-level. Therefore the aim of hospitals throughout the Netherlands is to arrange the COVID care in the best possible manner, but also assuring regular care to continue as much as possible. With this in mind, the research team decided not to further postpone the inclusion of the control group and planned implementation of the care-pathway is estimated at January 2021. We are aware of the changes in organisation of care that come with the periodical higher burden of COVID-care, so we plan to monitor changes in organisation at the Emergency Department during the inclusion period in each participating hospital.

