### 5.1.5 Sample size

We hypothesize that implementing the care pathway will reduce the mean ED-LOS with 10%. In a prospective study about the quality of Acute Care, by [name] (submitted for publication), the mean length of stay at the ED in the Maxima Medical Centre is three hours and twenty minutes (95% CI 3:00-3:40, SD=1.17). Assuming a normal distribution, a two sided test, power of 80% and a significance level ( $\alpha$ ) of 0.05, a minimum of 466 patients need to be included, 233 patients in both control and intervention group. We aim to include 300 patients in each group, with a estimated timeframe of one year. Each hospital will gather their own control-group before implementation of the care-pathway. A minimum number of control-patients will be established for each participating hospital, dependent of number of annual patient-visits at the Emergency Department.

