## 5.5 STATISTICAL ANALYSIS

Primary and secondary study parameters and endpoints are described in 'Study parameters/endpoints'. All statistical analyses will be performed with SPSS 24.0 for Windows (IBS, SPSS Statistics, Chicago, IL, USA). Descriptive statistics will be used for frequencies, percentages, means and standard deviations. Continuous variables will be analysed using independent t-tests, whereas the categorical data will be analysed by chi-square or Fisher's exact test. Median and interquartile ranges of non-normally distributed categorical and metric variables of the study will be

assessed using Mann-Whitey-U-test. Prevalence of the most frequent diagnosis (coded ICD-10) at discharge will be presented in percentages. HR and corresponding 95% confidence intervals will be calculated. Generalized Estimating Equations (GEEs) will be used, which adjust for observations made within the same hospitals being more alike. All tests will be performed using a significance level of  $\alpha = 0.05$ . A two-sided p-value  $< 0.05$  will be considered significant.

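### The stepped-wedge label has no steps or switch dates behind it: as described, ED-LOS is compared before versus after within hospitals, and the pathway effect cannot be separated from calendar time

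*Protocol*

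**What the plan says.** The Protocol's Summary (section 1) gives the design as "A longitudinal multi-centre cohort with a stepped-wedge cluster design". Nothing else in the document defines a step, a sequence, an order of hospitals or a set of staggered dates.

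The timing is in section 4 (Study design). On controls: "All hospitals agreed to restart inclusion of the control-group from August 2020 onward". On the pathway: "The planned start for implementation of the care-pathway is January 2021, dependent on inclusion of the control-group and the evolution of the COVID-pandemic". A later paragraph, written during the second wave, repeats that "planned implementation of the care-pathway is estimated at January 2021". It expects the COVID load to rise periodically and responds that "we plan to monitor changes in organisation at the Emergency Department during the inclusion period in each participating hospital". The same section records that one hospital "had started the care-pathway, but had to discontinue after a few weeks due to the massive burden of COVID-care"; this was before the control group was restarted.

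Section 5.1.5 has every hospital collect its controls before it implements the pathway, and adds: "A minimum number of control-patients will be established for each participating hospital, dependent of number of annual patient-visits at the Emergency Department". Section 5.3.1 aims to compare each hospital's controls with that hospital's own intervention patients.

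Section 5.5 states that "Continuous variables will be analysed using independent t-tests", lists the usual tests for other data types, and names GEE to allow for similarity of patients within a hospital. It mentions no period, season or calendar-time term.

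**The concern.** A stepped-wedge design separates an intervention from time because hospitals switch at different dates. In any given period some hospitals are still on usual care while others have switched, and the model carries a period effect. Without the stagger or the period effect, that protection is absent.

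Here the label promises the protection, but the described conduct does not provide it. If hospitals switch together, every control is earlier than every pathway patient. Crowding, staffing, season and COVID load may all move ED-LOS, a primary endpoint, and all may differ between late 2020 and 2021. A downward shift would be credited to the pathway. An upward shift of 20 min would cancel a true 20 min benefit. A reader who trusts the label would take the result as adjusted for time when it is not.

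**Working it through.** **Inputs from the Protocol, section 5.1.5.** Mean ED-LOS 3 h 20 min = 200 min; hypothesised reduction 10% = 20 min; SD printed as 1.17; two-sided alpha 0.05; power 80%; minimum 233 per group (466 in all); target 300 per group.

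**1. Reproduce the stated sample size.** n per group = 2 × (1.96 + 0.8416)² × (SD/20)².
- SD read as 1.17 h = 70.2 min: 15.70 × 3.51² = 193.4, so 194 per group (388 in all). This does not match.
- SD read as 1 h 17 min = 77 min: 15.70 × 3.85² = 232.7, so 233 per group (466 in all). This matches.

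The stated number is therefore a plain two-group calculation with SD 77 min, with no allowance for hospitals or time. I use 77 min below.

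**2. What a pure time shift does to the comparison.** Suppose the pathway has no effect and mean ED-LOS moves by s minutes between the control and pathway periods. SE = 77 × √(2/n), which is 7.13 min at n = 233 and 6.29 min at n = 300. The rejection probability is P(|Z + s/SE| > 1.96).

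| Assumed shift s | 233 per group | 300 per group |
|---|---|---|
| 5 min | 11% | 12% |
| 10 min | 29% | 36% |
| 15 min | 56% | 66% |
| 20 min | 80% | 89% |

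The nominal rate is 5%. The shifts are assumptions. At 20 min the figures equal the power for the hypothesised effect, because the two situations produce the same data. A GEE that handles only within-hospital correlation changes the standard error but leaves the shift in the estimate.

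**3. Can a period term rescue a common switch date?** Take 5 hospitals and 6 periods (assumed), all switching after period 3. The fixed part of the model has 7 columns: 6 period indicators and 1 pathway indicator. The pathway column is the sum of the indicators for periods 4, 5 and 6, so the matrix has rank 6 for 7 parameters. The pathway effect cannot be estimated.

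**4. What a real stepped wedge would deliver at this size.** Assumed: 5 hospitals, 6 equal periods, one hospital switching per step, equal cell sizes, a random hospital effect, fixed period effects, total SD 77 min. Power = Φ(20/SE − 1.96).

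| Total N | ICC | SE (min) | Power |
|---|---|---|---|
| 466 | 0.01 | 10.9 | 45% |
| 466 | 0.05 | 11.8 | 40% |
| 600 | 0.01 | 9.8 | 54% |
| 600 | 0.05 | 10.5 | 48% |

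Under the same assumptions 80% power needs about 1,230 patients (ICC 0.01) to 1,360 (ICC 0.05).

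**The case against.** - **Some stagger is likely.** January 2021 is planned and estimated, not fixed. It depends on control accrual, section 4 allows control inclusion to be extended, and section 5.1.5 sets a minimum per hospital. Hospitals may switch at different times and so overlap. This stands: a reader might infer a single fixed switch date, and the documents do not support that. But a stagger that follows local accrual or COVID load is not set in advance, may itself be related to ED crowding, and helps only if time is modelled.
- **A SAP may add a period term.** It may, and the absence of a covariate list would not be a fault by itself. Nor does section 5.5 say that the unadjusted t-test is the primary ED-LOS analysis. But steps and switch dates belong in the protocol, and under a common switch date no model can recover the effect.
- **The protocol did act on pandemic confounding.** A reader might take section 4 as conceding that the restarted comparison is heavily confounded. It does not. That sentence concerns pre-pandemic against post-pandemic populations and is the reason for restarting the controls. What remains is the expected periodic rise in COVID load, which is met by monitoring with no stated use in the analysis.
- **The hospital that began early.** A reader might infer that its new controls are contaminated. The pathway ran there only a few weeks and stopped before the restart, and nothing shows that any of it persisted. This justifies a sensitivity analysis, not a finding of contamination.
- **The shifts in the first table are invented.** They are assumptions and are labelled so. With SD 1.17 h the 10 min figure at 300 per group would be 41% instead of 36%.

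**Conclusion.** The point holds: the Summary claims a design property that the rest of the protocol does not deliver. What is described is a within-hospital before-after comparison that cannot separate the pathway's effect on ED-LOS from calendar time.

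The risk is structural. Given SD 77 min and an assumed shift of 10 to 20 min, false-positive rates would be 29% to 80% at 233 per group and 36% to 89% at 300. It would go too far to say that bias has been shown or that the result will be uninterpretable, because the documents give neither the size nor the direction of any shift. The stated 466 is arithmetically sound for a simple two-group comparison; it does not support 80% power for a time-adjusted stepped wedge under the assumptions above.

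**What to change.** In sections 1 and 4, remove the stepped-wedge label and state that the ED-LOS result is an uncontrolled before-after estimate, unless hospital-specific staggered switch dates are written into section 4 before implementation. Where dates do differ between hospitals, add calendar period to the GEE in section 5.5. Report a sensitivity analysis without the hospital that had briefly run the pathway.

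The monitored changes in ED organisation should not be added as an adjustment covariate: the pathway itself changes how the ED works, so adjusting could remove part of its effect. They can be reported descriptively.

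Cost: the first route needs only an amendment and a weaker stated conclusion. Modelling time widens the interval. Keeping the stepped-wedge claim is the expensive route. Section 5.1.5 must then restate its power with its own number of hospitals, periods and ICC. On the assumptions used here, the sponsor would accept about 40% to 54% power at the planned size or recruit roughly 1,230 to 1,360 patients, and hospitals that switch late would wait longer.

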## 5. STUDY POPULATION

### 5.1.1 Population

Older adult patients presenting with a non-specific main complaint at the practice of their general practitioner (GP) will be screened for inclusion. If a patient meets the inclusion criteria, the GP will refer the patient to a hospital that implemented the care pathway and notify the specialist at the ED (internist, ED-doctor or elderly care physician). Every referring care professional will have a card, which provides information on how to refer a patient to the care pathway and to whom. Patients not referred by the GP can enter the care pathway in several other ways:

- if referred by the practitioner at a nursing home
- if triage at the ED points to a NSC

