### **5.1.3 Exclusion criteria**

A potential subject who meets any of the following criteria will be excluded from participation in this study:

- Specific (main) complaint coupled to a diagnosis (pain, dyspnea, cough, localised weakness, swollen extremity, diarrhea, dysuria, bleeding, syncope, skin lesions, vertigo, palpitations, e.g.)
- Age <70 years
- Patient refusing data collection or participation in the care pathway

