### **5.1.4 Control group**

For patients included in the study as controls, the same inclusion and exclusion criteria apply.

Controls will not be specifically asked for informed consent, as each participating hospital will sign a form to collect data for control patients prior to implementing the care pathway. Additionally, it is the responsibility of each participating institution to inform their patients on the policies regarding data collection in study settings.

Obtaining the retrospective control-group will be done by CTcue, if possible. CTcue is a search engine in which unstructured data from an Electronic Health Record (EHR) can be easily found by adding specific queries in to the search engine. These data will be retrieved anonymously according to our defined in- and exclusion criteria, study parameters and endpoints. Specialists at the ED will be unaware of the patients functioning as controls during this study, since data for controls will be collected retrospectively. After 30 and 90 days, the research nurse will evaluate complications that occurred after the patient leaves the care pathway.

In the participating hospitals without access to CTcue, control patients will be gathered prospectively. The ED specialist will save the patient-number of eligible patients in the care pathway (before it is implemented). The specialist in charge of the patient is allowed to use patient data for research, without consent when data is anonymised. The specialist may grant this right to a third party, in this case the research team. This exchange of data has to be approved by the involved departments, which will be the department of Internal Medicine, Geriatrics and the Emergency Department.

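### Eligible patients are identified differently before and after the pathway starts, so a difference in ED length of stay may partly reflect selection

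*Protocol*

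**What the plan says.** **Intervention period.** A patient reaches the pathway through a GP, a nursing-home physician or ED triage (Protocol Section 5.1.1). Two more steps follow before inclusion: "If the ED specialist registers access to the care pathway and the patient gives consent, the patient will be included and baseline data collected" (Section 1, Recruitment). Section 5.1.3 lists as an exclusion: "Patient refusing data collection or participation in the care pathway".

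**Control period.** Section 5.1.4 says: "For patients included in the study as controls, the same inclusion and exclusion criteria apply". The same section adds: "Controls will not be specifically asked for informed consent". The method of finding controls depends on the hospital. Where the search engine is available, "Obtaining the retrospective control-group will be done by CTcue, if possible". Elsewhere, "In the participating hospitals without access to CTcue, control patients will be gathered prospectively", with the ED specialist keeping the patient numbers of those who qualify. Section 5.3.1 repeats this split and intends each hospital's controls to be compared with its own intervention patients.

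**Referral.** Section 5.1.1 says of a patient who meets the criteria that "the GP will refer the patient to a hospital that implemented the care pathway".

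**Analysis.** Section 5.5 names t-tests, chi-square or Fisher tests, Mann-Whitney tests, and GEE to account for similarity within hospitals.

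**The concern.** In a before-and-after comparison within hospitals, the two groups must be found in the same way. Otherwise the difference in means mixes the effect of the pathway with the effect of who was counted. Here the intervention group has passed filters that some or all controls did not pass.

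Consent applies in every hospital. It is unlikely to be lost at random, because disorientation, behavioural change and cognitive decline are qualifying complaints (Section 5.1.2), and a patient without capacity needs a legal representative's consent (Section 6.3). Recognition and registration are a further difference at CTcue hospitals.

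ED-LOS is a primary endpoint with a small target effect, so a modest shift in case mix matters. More patients do not remove this kind of bias. The Protocol describes no step that keeps data on eligible patients who were not registered after the switch.

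**Working it through.** **1. Steps to inclusion, side by side**

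| Step | Intervention period | Controls, CTcue hospitals | Controls, other hospitals |
|---|---|---|---|
| Recognition | GP, nursing-home physician or triage | Record query | ED specialist |
| Registration | ED specialist | None | ED specialist saves the patient number |
| Consent | Required | Not asked | Not asked |
| Refusing the pathway | Excluded | Cannot occur | Cannot occur |

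A control might still object to data use under the hospital's own information policy. Refusing participation cannot occur before there is a pathway to refuse. That half of the Section 5.1.3 criterion therefore cannot apply to controls, contrary to the equal-criteria statement in Section 5.1.4.

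**2. The plan's own figure (Section 5.1.5)**

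Mean 3 h 20 min = 200 min; a 10% reduction is 20 min = 0.333 h. Two-sided alpha 0.05, power 80%.

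n per group = 2 × (1.960 + 0.842)² × SD² / 0.333²

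- SD read as 1 h 17 min (1.283 h): 2 × 7.849 × 1.647 / 0.1111 = 232.7, so 233 per group and 466 in total. This matches the Protocol.
- SD read as 1.17 decimal hours: 194 per group and 388 in total, which does not match.

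The first reading is used below. At the intended 300 per group, SE = 1.283 × √(2/300) = 0.105 h = 6.3 min.

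**3. Formula for the bias**

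Let f be the fraction of eligible patients not captured and D their mean ED-LOS minus that of captured patients. The captured mean is then f × D below the mean of all eligible patients. With no pathway effect and no change over time:

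apparent reduction = (f × D in the intervention period) − (f × D in the control period)

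If control capture is complete, the second term is zero and the bias is f × D.

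**4. Illustration**

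The documents give neither f nor D, so these values are assumed. The false-positive probability is Φ(b/SE − 1.96) + Φ(−b/SE − 1.96), with b the bias, 300 per group, no true effect and no allowance for clustering.

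| f | D | Bias | Share of 20 min | False-positive probability |
|---|---|---|---|---|
| 10% | 15 min | 1.5 min | 7% | 5.7% |
| 20% | 30 min | 6 min | 30% | 16% |
| 30% | 30 min | 9 min | 45% | 30% |
| 30% | 60 min | 18 min | 90% | 82% |
| 50% | 60 min | 30 min | 150% | above 99% |

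If D is negative, the sizes are the same but the bias runs against the pathway.

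**The case against.** Much can be said against a broader claim, and most of it stands.

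- **A reader might infer that all controls are found by record search.** They are not. Hospitals without CTcue have the ED specialist log them, so recognition and logging occur in both periods there. What remains is consent and the entry route. The number of CTcue hospitals is not stated, and a text query is not shown to find every eligible attender.
- **A reader might infer that intervention patients are enrolled in quieter hours.** Both groups share the weekday 11:00–20:00 window (Section 1), and nothing in the Protocol links registration to crowding.
- **A reader might infer that GPs will drain control-phase hospitals.** Section 5.1.1 can be read that way only if hospitals switch at different times. Section 1 calls the design stepped-wedge, but Section 4 gives one control restart (August 2020), one planned pathway start (January 2021) and no step schedule. A change in case mix is possible, not established.
- **Confused patients are not simply lost.** Section 6.3 provides for consent through a representative.
- **Adjustment is possible.** Age, complaint category, way of arrival and living situation are recorded (Section 5.4.1), and an SAP may name them as covariates in the GEE.

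The last point helps only in part. Covariates adjust for measured differences among patients who are in the data set; they do not bring back eligible patients who were never recorded. The other points narrow the concern without removing it.

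**Conclusion.** The point holds as a difference in ascertainment that the Protocol itself fixes. At every hospital, consent and refusal filter the intervention group only. At CTcue hospitals, recognition and registration differ as well. The statement that the criteria are the same for controls cannot be met for refusal of participation.

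The size and direction of the bias cannot be derived from the documents. On the assumed inputs it runs from 1.5 min, which is negligible, to 30 min, which exceeds the 20 min target. These figures assume complete control capture.

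It is tempting to conclude that missed patients stay longer, so that the pathway is flattered. Section 2 does link undertriage to prolonged stay. But Section 1 also says that patients with non-specific complaints stay longer; if the clearest such cases are the ones recognised, the bias would go the other way. The documents do not settle this, nor do they show an effect on mortality or readmission.

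The matter should be settled before the intervention period, because a log that was not kept at a non-CTcue hospital cannot be rebuilt reliably.

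**What to change.** 1. **Same ascertainment in both periods.** At CTcue hospitals, run the identical query for the weekday 11:00–20:00 window before and after the switch date. Elsewhere, keep the same ED patient-number log in both periods.
2. **Primary ED-LOS analysis.** Compare all eligible attenders by period, whether or not they were registered in the pathway, on the routine-data basis already used for controls. Exclude, in both periods, only those who object to use of their data. Reword Sections 5.1.3 and 5.1.4 so that refusing data use and declining the pathway are separate matters.
3. **Supportive analysis.** Report registered, consenting patients separately, with the number eligible and the number registered per hospital, so that f is known.
4. **Referral.** If hospitals switch at different times, the postal code already collected (Section 5.4.1) allows an optional sensitivity analysis. It first needs hospital catchments, which the Protocol does not define.

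**Cost.** A repeat of an existing query, continued logging at the non-CTcue hospitals, and METC notification that routine data are used on the same basis in both periods. If uptake is incomplete the estimated effect will be diluted, but it then describes the effect of implementing the pathway, which is the stated objective. The change serves ED-LOS and other outcomes taken from routine records; it does not address patient satisfaction, which depends on a questionnaire.
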